## Abstract

**Background:**

Survival in cancer patients has increased exponentially in recent years, with multiple side effects caused by treatments. Cancer-related asthenia and dyspnea are among them, which represent a serious health problem, with considerable limitations and reduced quality of life. An implementation of the conventional clinical practice, developed through physical exercise, may be useful in controlling dyspnoea. This study aims to compare the effects of a comprehensive rehabilitation implementing a programme of multimodal physical exercise with a specific autonomy recovery programme, versus an isolated intervention using the physical exercise programme alone, on the functionality, physical performance and respiratory parameters in oncologycal patients with dyspnea.

**Methods:**

This is a protocol por an experimental, prospective, randomized, parallel-controlled clinical trial, with two arms design of fixed assignment with an experimental and control groups. It will conduct in the Oncology Hospitalisation Unit at the University Hospital Complex of Salamanca, using consecutive sampling to select 50 participants with oncological dyspnoea who are hospitalised at the time of inclusion. After baseline assessment, participants will be randomised into the groups. Experimental group will complete Comprehensive Rehabilitation with the autonomy recovery and the multimodal exercise programmes, and in the control group, only the multimodal exercise programme will be carried out. The primary outcomes will be basic activities of daily living (Barthel Index) and degree of dyspnoea (MRC scale). Additionally, physical performance will be evaluated with the Short Physical Performance Battery (SPPB), as will the oxygen saturation in the blood using pulse oximetry, fear/avoidance of movement with the Tampa Scale of Kinesiophobia (TSK), and the quality of life of the oncology patient (ECOG performance scale).

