#### Sample size

The sample size has been estimated based on the potential modification of the most stringent of the principal variables of the study—the score on the Barthel Index. For this, as a reference, we have used the results obtained in a study with similar characteristics, in which the scoring on the Barthel Index was modified by 7.5 points [17]. With these premises, accepting an alpha risk of 0.05 and a beta risk of 0.2 in a bilateral contrast, we will need 25 subjects in the first group and 25 subjects in the second group in order to detect a difference greater than or equal to 7.5 units. The assumed common standard deviation is 8.3. We estimate a rate of 20% lost to follow-up. The sample size was estimated using the programme EPIDAT 4.2.

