#### Description of the variables

For the principal variable being manipulated, we will study dyspnoea (Medical Research Council, MRC) and the degree of dependence in carrying out the activities of daily living (Barthel Index, BI). And as secondary variables, we have the patient’s physical performance (via the Short Physical Performance Score, SPPB), their fear/avoidance of movement (Tampa Scale of Kinesiophobia–Fatigue, TSK-F), the oxygen saturation in the blood (pulse oximetry), and the quality of life of the oncology patient (ECOG performance status scale). Other intervening variables include those gathered from the patient’s clinical history, such as pathological diagnosis, number of lines of treatment, and socio-demographic and anthropometric data (sex, age, weight, height, and BMI).

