#### Tools employed in the evaluation of the variables

“Barthel Index, (BI)” [18]: to evaluate dependence. Measures physical disability with proven validity and reliability. It is easy to apply and to interpret. Useful for evaluating the patient’s functional independence in the activities of daily living (ADL). Scored from 0 to 100, it quantifies the individual’s degree of dependence.“Medical Research Council dyspnoea scale (MRC)” [19], to evaluate dyspnoea. The aim is to make it possible for the patients to quantitatively grade their own dyspnoea in a simple, visual manner. It establishes 5 degrees of dyspnoea when carrying out activities.“Short Physical Performance Score (SPPB)” [20], to evaluate physical performance. The short physical performance battery, proven in our area for primary health care, is a test designed specifically to predict disabilities, and it has demonstrated the capacity to predict adverse events, dependence, institutionalisation, and mortality.The “Tampa Scale of Kinesiophobia–Fatigue (TSK-F)” [8, 9], was developed to evaluate the fear of movement related to fatigue/pain. It has been proven effective in oncology patients and those with chronic fatigue syndrome. We will use the model with 11 items (TSK-F-11).“Pulse oximetry” [21]: a non-invasive technique which uses a pulse oximeter to measure the saturation of oxygen (Sat O_2_) in the haemoglobin in circulating blood, usually in arterial blood.“ECOG performance status scale” [22], is a practical way to measure the quality of life of cancer patients, whose life expectancies may change within a period of months, weeks, or even days. It was designed by the Eastern Cooperative Oncology Group (ECOG) in the United States and validated by the World Health Organization (WHO). The primary function of this scale is to objectify the patient’s quality of life or performance status.

The variables will be recorded on an individual sheet for each patient and stored afterwards in a database designed specifically for this study.

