### Data analysis

The statistical analysis will be carried out with the intention to treat. In the descriptive analysis, the population is described by presenting the data as means and standard deviations for the continuous variables and as frequency distributions for the qualitative variables. To evaluate the comparability in the baseline assessment between the two study groups, we will employ the Chi-squared test for qualitative variables and the Student’s T-test for the comparison of the means between the two groups, in addition to the Kolmogorov–Smirnov test to find the normality of the sample. In the inferential analysis, we will consider a confidence interval of 95% (*p* < 0.05), and will use Student’s T-test for related pre and post samples and for independent samples at the end of the study, in addition to a multivariate analysis of variance (MANOVA) with repeated measures (3 levels) to assess interactions between categorical variables, and to determine significant differences between groups and within groups. Additionally, to assess the magnitude of the change in the variables, the effect size of the interventions will be calculated as Cohen’s d (small (0.2), medium (0.5), and large (0.8)) and the partial eta squared (ƞ2p) (small (0.01), medium (0.06), and large (0.14)), where significant, as appropriate with the statistical test applied [25]. We will use Pearson’s Correlation Coefficient to analyse the correlations between the various intervening variables and the parameters established in the different questionnaires and scales employed. A survival follow-up analysis will be completed using the Kaplan–Meier non-parametric method to learn the time of the intervention until the patient’s discharge from hospital, and the survival curves of each of the groups in the study will be compared using the non-parametric logrank test. Processing and analysing the data will be done using the statistics pack SPSS 25.0.

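### Two unranked primary outcomes are tested at an unadjusted 0.05 by overlapping between-group tests; if either outcome counts as success, the risk of a false primary claim is about 9–10%

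*Protocol article*

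**What the plan says.** Two outcomes are primary. The abstract (Methods) says: "The primary outcomes will be basic activities of daily living (Barthel Index) and degree of dyspnoea (MRC scale"). The section on description of the variables repeats the pair as the principal variable: "we will study dyspnoea (Medical Research Council, MRC) and the degree of dependence in carrying out the activities of daily living (Barthel Index, BI"). Neither place puts one ahead of the other.

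The sample size section works from Barthel only, calling it "the most stringent of the principal variables of the study". It gives the error rates as "accepting an alpha risk of 0.05 and a beta risk of 0.2 in a bilateral contrast", the target as "to detect a difference greater than or equal to 7.5 units", and adds: "The assumed common standard deviation is 8.3". It gives no effect size, standard deviation or power for MRC.

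The data analysis section sets p < 0.05 for the inferential analysis as a whole. It lists paired t-tests before and after, and a t-test "for independent samples at the end of the study, in addition to a multivariate analysis of variance (MANOVA) with repeated measures (3 levels"). The MANOVA is meant to show interactions and differences both between and within groups. The article does not divide or order the 0.05, does not say whether one or both primaries must be significant, and does not say which between-group test decides.

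**The concern.** A two-sided 0.05 limits the false-positive risk to 5% for one outcome and one test. Here one outcome and one test were used for sizing, while two outcomes carry primary status and at least two kinds of between-group test are planned at the same threshold. Someone following the text could report a positive primary result from Barthel or from MRC, and from the t-test or the MANOVA. The chance that at least one is significant when the autonomy programme adds nothing is then above 5%. If the tests disagree, nothing in the article says which one stands. What is at stake is what counts as a positive trial, and that cannot be settled credibly once results are known.

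**Working it through.** **Inputs from the protocol article.** Difference 7.5, SD 8.3, two-sided alpha 0.05, power 80%, 20% loss, 25 per group (sample size section); two primary outcomes (abstract; description of the variables); p < 0.05 per test and three assessments (data analysis section).

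**Assumed, because the article does not give them.** Correlation between the two outcomes' test statistics, 0 to 0.9. For the simulation: correlation between visits 0.3 to 0.9, correlation between outcomes 0 to 0.5, and normally distributed scores.

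**1. The plan's own figure.** n per group = 2 × [8.3 × (1.960 + 0.842) / 7.5]² = 19.2, so 20. Allowing for 20% loss, 20 / 0.8 = 25. This matches the stated 25 per group. The sizing is right for one outcome and one test.

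**2. Two outcomes, one test each, either one counting.** If independent, 1 − 0.95² = 9.75%; the upper bound is 2 × 0.05 = 10%. From the bivariate normal distribution:

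| Correlation | Either significant | Both significant |
|---|---|---|
| 0 | 9.75% | 0.25% |
| 0.3 | 9.5% | 0.5% |
| 0.5 | 9.1% | 0.9% |
| 0.7 | 8.3% | 1.7% |
| 0.8 | 7.8% | 2.2% |
| 0.9 | 7.0% | 3.0% |

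The last column is the rate when neither outcome has an effect. If one outcome has a true effect and the other has none, a both-required rule still errs at most 5% of the time.

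**3. Adding the MANOVA, run separately for each outcome, with any listed test counting.** Four independent tests would give 1 − 0.95⁴ = 18.5%, with an upper bound of 4 × 0.05 = 20%. The tests on one outcome are in fact correlated, so this was simulated under no effect (25 per arm, three visits, 20,000 trials per setting):

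- Final t-test only, either outcome: 9.0–10.0%.
- Final t-test or group-by-time interaction, either outcome: 16.4–18.3%.
- The same, or the MANOVA group main effect: 19.3–22.5%.

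**4. Within-group tests.** In one setting (visit correlation 0.5, outcome correlation 0.3), both arms improved by 0.5 SD from baseline to the final assessment, with no difference between arms. Counting the experimental arm's paired t-test as well, at least one test was significant in 89% of trials. A pre-post test therefore cannot serve as evidence for the added programme.

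**5. What each rule would need.**

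- *Alpha split to 0.025 per outcome.* Barthel needs 24 evaluable per group (25 by the t distribution): 24 / 0.8 = 30, or 25 / 0.8 = 31.25, so 32 recruited, against 25 planned. With 20 evaluable per group, power at 0.025 is 70%.
- *Both required at 0.05.* Joint power cannot exceed the lower of the two powers. If each were 80% and independent, it would be 0.8 × 0.8 = 64%.
- *Barthel first, then MRC.* Barthel keeps the full 0.05 and its planned power. If Barthel has no true effect, a false claim on either outcome needs a false-positive Barthel test first, at most 5%. If Barthel has a true effect, the only possible false claim is on MRC, again at most 5%.

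**The case against.** The strongest reply is that a success rule and a decisive test are commonly left to the analysis plan, and only an article is at hand. Silence on those two items alone would be no finding. What stands is what the article does fix: two equal primaries, one unadjusted threshold, overlapping between-group tests, and a sample size with no alpha reserved for a second primary.

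Three stronger readings are tempting and are not supported.

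- A reader might infer that the trial's error rate simply is about 20% instead of a promised 5%. The article promises no familywise 5%: its 0.05 is the sizing alpha for Barthel and a per-test level. Nor does it say that either outcome suffices. Under a both-required rule alpha is at most 5% with no adjustment, and the remark that Barthel is the most demanding principal variable could be read as an intention to cover both.
- A reader might take it that each primary gets its own MANOVA. The data analysis section does not say so. If Barthel and MRC enter one joint model, the 16–22% range does not apply.
- A reader might add that MRC is the more bias-prone outcome, since its purpose is "to make it possible for the patients to quantitatively grade their own dyspnoea" and patients are not blinded. That has no bearing on multiplicity. The comparison is also unsupported, because the article does not say how Barthel ratings are obtained.

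**Conclusion.** The point holds in conditional form. With two unranked primaries, one test each at 0.05, and either counting, the false-claim risk is about 9–10% for correlations up to about 0.5, falling to 7–8% at 0.8–0.9. The range of roughly 16–22% needs two further assumptions: a separate MANOVA for each outcome, and success on any of the between-group tests. It also depends on correlations that the article does not give. A both-required rule would hold alpha at or below 5%, but the article gives no basis for power under it. The defect is that the text permits rules with quite different error rates and powers, while the sample size fits only a primary claim that rests on Barthel at the full 0.05.

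**What to change.** Before unblinding, state in the protocol and analysis plan:

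- one named between-group test per primary outcome as the decisive one;
- Barthel tested first at two-sided 0.05, consistent with the existing 25 per group;
- MRC tested second at two-sided 0.05, only if Barthel is significant;
- all other tests, including the remaining MANOVA effects and the within-group pre-post t-tests, labelled secondary or exploratory.

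This needs no extra patients and no change to data collection. It costs a change of wording and an update of the registry entry. The real price is that MRC cannot be claimed as confirmatory if Barthel fails, which matters in a trial recruited on dyspnoea. If the investigators prefer to require both outcomes, alpha is also controlled, but they should then justify the sample size for both.

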**Discussion:**

The results of this study may be translated to clinical practice, incorporating a specific autonomy recovery programme into comprehensive rehabilitation programmes of care for cancer patients with dyspnoea. Increase in the survival of patients with cancer includes multiple side effects as cancer-related asthenia and dyspnea, which represents a serious health problem. The current study addresses to improve the conventional clinical practice by proposing an integral, rehabilitative approach, to implement education and training for oncology patients with dyspnea to increase their quality of life.

**Trial registration:**

ClinicalTrials.gov; ID: NCT04766593. (February 23, 2021).

## Background

In recent years, the improvement in cancer treatments and broad support for preventive strategies have enabled us to reach a higher rate of early diagnosis and a better understanding of the oncologic pathology itself, thus achieving an exponential increase in the five-year survival of patients with cancer [1].

Linked to that increase in survival, and due to the resulting increase in the lines of treatment employed, we are seeing greater side effects, which have repercussions in aspects such as the patients’ functionality and their quality of life [2]. Some of these side effects include cancer-related asthenia, anxiety, and dyspnoea [3]. Dyspnoea may represent a serious health problem, with considerable limitations for the individuals. In some patients with advanced-stage cancer, this dyspnoea may represent a clinical sign of the final phase of the disease [4]. Approximately 41% of the patients in palliative care have dyspnoea, and 46% of those describe it as being moderate or severe [5, 6].

The majority of patients perceive this dyspnoea to be a limiting factor that is out of their control, which leads them to adopt behaviours which have negative repercussions on their functionality [7], such as cancer patients creating patterns of fear/avoidance of movement or of physical activity, as is often the case also with patients with chronic pain, chronic fatigue syndrome, or fibromyalgia [8, 9]. It is similar to when patients with respiratory problems decrease their level of activity to adapt to their symptomatology. This favours a worsening of their physical state and of the dyspnoea upon exertion, known as the “cycle of the respiratory patient” [10].

To control the dyspnoea, we believe that the measures employed in conventional clinical practice, which have been mainly developed through physical exercise, may be implemented. Reeducation and work on the activities of daily living, together with a programme of physical exercise, as part of an integral approach of functional reeducation, may be a good intervention for dyspnoea in oncology patients [11]. For this reason, in this clinical trial we are proposing an intervention with an integral perspective that is based on a rehabilitative approach, with the objective of integrating education and training of the oncology patient with dyspnoea in the adaptation of their day-to-day activities while their cardiopulmonary reserves are gravely reduced, with the aim of recovering their capacity to carry out their occupational roles.

After analysing previous studies, we have observed that the most-employed intervention is physical exercise, which has been shown to give good results in the majority of dyspnoea cases [12, 13]. Additionally, it appears that multimodal physical exercise programmes, which combine different types of exercise, such as aerobic exercise and strength training primarily, appear to have better overall results in cancer patients [14–16]. However, there are not many studies which correlate whether this improvement in symptoms has had positive repercussions on the patients’ functionality when carrying out their activities of daily living. We believe that, in addition to employing physical exercise to improve the patients symptomatology, this intervention should be geared towards increasing the individuals autonomy, and that this will make it possible to generalise in their daily life the symptomatic clinical effects obtained through the therapeutic process, which will be inexorably linked to an improvement in their quality of life.

As such, we are proposing as an intervention an Oncological Functional Reeducation Programme, to be used in addition to the intervention with physical exercise. It would be a reeducation in the completion of the activities of daily living, so as to foment the recovery of personal autonomy, and thus to observe to what degree this improves the results in clinical practice. The findings will provide important insight into the development of an effective care model with a comprehensive rehabilitation programme that includes a specific autonomy recovery programme in oncological patients with dyspnoea.

## Methods/design

### Aims

In accordance with that laid out above, the primary aim of this study is to contrast our hypothesis, that the intervention using a specific programme for the recovery of autonomy by means of reeducation on the activities of daily life, when added to multimodal physical exercise, will increase the beneficial effects of physical exercise as an isolated intervention on the functionality, physical performance, and respiratory parameters in oncology patients with dyspnea. The objectives seek to compare the effects produced by the implementation of a programme of multimodal physical exercise and a specific programme for recovering autonomy, with an isolated intervention using physical exercise, on the functionality and physical performance of cancer patients with dyspnoea.

### Design

This study is an experimental, prospective, randomized, parallel-controlled clinical trial, with two arms design of fixed assignment with an experimental and a control groups. It will conduct during a year in the Oncology Hospitalisation Unit at the University Hospital Complex of Salamanca (CAUSA), using consecutive sampling to select the participants with oncological dyspnoea who are hospitalised at the time of inclusion.

### Sample/participants

#### Participants

The patients will be recruited from the Oncology Hospitalisation Unit at the CAUSA, and must meet the following selection criteria: A) Inclusion criteria: Participants must have a pathological diagnosis of an oncological disease, be over 18 years of age, be hospitalised at the time of recruitment in the Oncology Unit at CAUSA, meet dyspnoea parameters of 2 or more points on the Medical Research Council scale (MRC), receive fewer than 85 points on the Barthel Index, and have signed an informed consent form indicating voluntary agreement to participate in the study. B) Exclusion criteria: not having an adequate cognitive state to be able to comprehend and follow the orders provided (fewer than 23 points on the Mini Mental State Examination, MMSE), having a haemoglobin level lower than 10 g/dL, being an active smoker at the time of recruitment. C) Withdrawal criteria: disease progression which brings the patient to a terminal situation or to death, and non-completion of the follow-up and final assessments.

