### Procedures and data collection

#### Evaluations and study plan

Three assessments will be completed in this study: one at the beginning, another after 7 days, and a final one before the patient is discharged from hospital. After recruitment and before randomisation and assignment to the corresponding group, all individuals will complete a baseline assessment (BA), which includes recording the independent variables and the variables of the primary and secondary results of the study. Then, while the patients are still in hospital, the subjects will be randomly assigned to the control or the experimental group, with the corresponding intervention applied in each of them. Later, two more assessments will be completed, one after 7 days, considered to be the follow-up assessment (FUA), and another at the time of discharge from the hospital, considered to be the final assessment (FA). This can be observed in more detail in Table 1.

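### Patients who leave hospital before day 7 can be randomised, and the plan does not say how they are handled when the day-7 assessment cannot take place before discharge

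*Protocol article*

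**What the plan says.** In the Protocol article, the Participants section introduces its list as the criteria that patients must meet. The only condition on hospital stay is to "be hospitalised at the time of recruitment in the Oncology Unit at CAUSA". The Design section repeats it: "using consecutive sampling to select the participants with oncological dyspnoea who are hospitalised at the time of inclusion". The exclusions are a low cognitive score together with "having a haemoglobin level lower than 10 g/dL, being an active smoker at the time of recruitment". None of them concerns planned discharge or expected remaining stay.

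The Evaluations and study plan section sets three assessments: "one at the beginning, another after 7 days, and a final one before the patient is discharged from hospital". It calls the second the follow-up assessment and the third the final assessment, and the interventions are applied while patients are in hospital.

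The withdrawal criteria in the Participants section are progression to a terminal situation or death, and "non-completion of the follow-up and final assessments".

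The Data analysis section plans intention to treat, paired pre-post t-tests, an independent-samples t-test at the end of the study, a repeated-measures MANOVA with three levels, and a Kaplan–Meier and logrank analysis of time to discharge. The Sample size section arrives at 25 per group and adds: "We estimate a rate of 20% lost to follow-up".

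**The concern.** The entry criterion and the visit schedule do not fit each other. The schedule assumes that day 7 comes before discharge, but nothing at entry makes this likely for a given patient, and the text gives no rule for a discharge that comes first.

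Three things are at stake.

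- **Repeated-measures analysis.** A standard repeated-measures MANOVA uses complete profiles only. A patient without a day-7 value drops out of it.
- **Intention to treat.** If missing the day-7 visit alone counts as non-completion, a patient who simply went home on time is withdrawn after randomisation. The criterion joins the two assessments with "and" and does not say whether missing one is enough.
- **Exposure.** The experimental component relies on daily training, a daily diary and daily supervision. A patient who leaves after a few days has received little of it.

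The protocol also compares time to discharge between the arms, so it treats length of stay as variable and possibly affected by the intervention. If stay does differ by arm, the share with no day-7 value would differ by arm too.

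**Working it through.** **1. Schedule against analyses.** Taking the texts as written:

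| Discharge, counted from baseline | Day-7 assessment | Discharge assessment | End-of-study t-test | 3-level MANOVA |
|---|---|---|---|---|
| Before day 7 (e.g. day 4) | Not possible before discharge | Available | Can enter | Profile incomplete |
| On day 7 | Same day as discharge | Available | Can enter | No distinct middle level |
| After day 7 | Available | Available | Can enter | Complete |

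The first two rows are eligible under the stated criteria.

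**2. The plan's own sample size.** Inputs from the Sample size section: difference 7.5, SD 8.3, two-sided alpha 0.05, beta 0.2, loss 20%.

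- n per arm = 2 × (1.960 + 0.842)² × 8.3² / 7.5² = 2 × 7.85 × 1.225 = 19.2, rounded up to 20.
- With 20% loss: 20 / 0.8 = 25 per arm, which matches the plan.
- With the t distribution, n = 20.23, and 20.23 / 0.8 = 25.3.

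The arithmetic is sound. It is a comparison of two means, so it corresponds to the end-of-study t-test. It leaves almost no spare patients beyond the 20% allowance.

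**3. Share leaving before day 7.** The article gives no length of stay, so everything in this step is assumed. Two shapes were used for remaining stay after baseline:

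- exponential: P(stay < 7) = 1 − 2^(−7/median)
- log-normal with log-SD 0.8: P(stay < 7) = Φ(ln(7/median) / 0.8)

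| Assumed median remaining stay | Exponential | Log-normal |
|---|---|---|
| 7 days | 50% | 50% |
| 10 days | 38% | 33% |
| 14 days | 29% | 19% |

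The median at which the share equals 20% is 7 × ln 2 / (−ln 0.8) = 21.7 days (exponential) or 7 × exp(0.8416 × 0.8) = 13.7 days (log-normal). Longer medians give smaller shares.

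**4. Power if patients are actually lost.** Normal approximation, 25 randomised per arm, loss from all causes together:

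| Total loss | Evaluable per arm | Power | Randomised per arm for 80% power |
|---|---|---|---|
| 20% | 20 | 0.815 | 25 |
| 30% | 17.5 | 0.76 | 29 |
| 40% | 15 | 0.70 | 34 |
| 50% | 12.5 | 0.62 | 40 |

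This table applies to early discharges only if they are withdrawn or the analysis requires all three assessments. If they stay in the discharge comparison, they do not count as losses.

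**The case against.** The strongest reply is that most of the loss does not follow. The final assessment takes place at discharge, whenever that is, so a patient who leaves on day 4 supplies both values that the paired and end-of-study t-tests need. This stands. A reader might infer that short-stay patients yield no primary outcome, or that early discharge uses up the 20% allowance before any death or drop-out. The documents do not support either inference, because both depend on reading the withdrawal criterion so that one missed visit is enough, or on requiring complete three-point profiles.

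It also stands that the documents do not show how many such patients there will be. They show that patients about to leave can be randomised, not that they are. If consecutive sampling means approaching patients as they are admitted, late recruitment could be uncommon. The idea that early leavers are the fitter patients is likewise an inference; entry already requires a Barthel score below 85 and an MRC grade of 2 or more. And a range of 19% to 50%, built on assumed medians and shapes, cannot by itself establish a material problem.

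A last argument is that handling of missed visits belongs in an analysis plan or full protocol. This holds for detailed missing-data methods. It does not remove the mismatch, because eligibility, schedule and withdrawal criteria are all set out in this article and do not agree. Table 1 and Fig. 1 could not be read for this check. If either gives a rule for discharge before day 7, that part of the point is met.

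**Conclusion.** The point holds as a mismatch between the eligibility criteria, the assessment schedule and the analysis. Following the text exactly, a randomised patient who leaves before day 7 has an incomplete profile for the MANOVA and, on one reading of the withdrawal criterion, is removed despite the intention-to-treat statement. The comparison at discharge is not lost for that patient unless that reading is applied.

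The size is unknown. The 19% to 50% range rests wholly on assumed medians of 7 to 14 days and two assumed distributions. If total losses did reach 30% to 40%, power would be about 0.76 to 0.70 instead of 0.815. The point deserves correction because the wording permits an avoidable post-randomisation exclusion and the main remedy costs little. It does not show that the trial is underpowered or that the 25 per arm is wrong.

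**What to change.** Reconcile the Participants, Evaluations and study plan, and Data analysis sections.

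**(a) Rule for discharge before day 7.** State that it is not a withdrawal, that the discharge assessment is that patient's final assessment, and that the patient stays in the primary between-group comparison at discharge. Clarify in the withdrawal criterion whether missing one assessment or both is meant. For the repeated-measures analysis, use a method that retains patients with a missing day-7 value, for example a linear mixed model in place of the complete-profile MANOVA. This costs a change of wording and of model, with no extra staff or visits.

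**(b) Where recruitment allows, an entry condition.** Require an expected remaining stay of at least 7 days from baseline, as judged by the treating team and recorded before randomisation. The cost is fewer eligible patients, in proportion to the share of short stays. If 19% to 50% would leave early and the prediction were accurate, the number to screen rises by a factor of 1/0.81 = 1.2 to 1/0.50 = 2.0, in a single unit recruiting 50 patients with the study planned to run for one year. It also narrows the population for the time-to-discharge analysis, and as a change of selection criteria it has to be notified to the ethics committee. Predicted stay is fallible, so (a) is needed whether or not (b) is adopted.
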